## Abstract

Patella alta is a clinical condition where the patella is positioned too proximal in relation to the femoral trochlea. Such an abnormality may cause patellar instability and predispose to recurrent patellofemoral dislocations and patellofemoral pain. There are no conclusive guidelines for determining a threshold for too high positioned patella, as several different methods have been described to measure patellar height. As a surgical solution, distalising tibial tubercle osteotomy has been described to correct excessive patellar height. In the early phase of the distalising tibial tubercle osteotomy postoperative protocol, weightbearing and knee flexion are limited with a brace commonly for 4–8 weeks to avoid potential implant failure leading to displacement of the osteotomy or non-union. The potential risks for adverse effects associated with the limitation rehabilitation protocol include a delay in regaining knee range of motion, stiffness and muscle weakness. As a result, recovery from surgery is delayed and may lead to additional procedures and long-term morbidity in knee function. This is a prospective, randomised, controlled, single-blinded, single centre trial comparing a novel accelerated rehabilitation protocol with the traditional, motion restricting rehabilitation protocol. All skeletally mature patients aged 35 years and younger, referred to as the distalising tibial tubercle osteotomy procedure group, are eligible for inclusion in the study. Patients will be randomised to either the fast rehabilitation group or the traditional rehabilitation group. Patients with patellar instability will be additionally treated with medial patellofemoral ligament reconstruction. The hypothesis of the trial is that the novel accelerated rehabilitation protocol will lead to faster recovery and improved functional outcome at 6, 12 and 24 weeks compared with the conservative rehabilitation protocol. A secondary hypothesis is that the complication rate will be similar in both groups. The study will document short-term recovery and the planned follow-up will be 3 years. After the 1-year follow-up, the trial results will be disseminated in a major peer-reviewed orthopaedic publication. Protocol version 3.6, date 28/11/2023.

## Introduction

The term patella alta refers to the abnormal height of the patellar, where the anatomical position of the patellar is too proximal. In cases of patella alta, patellar and trochlear cartilage surfaces have limited or no contact. This anatomical variation can cause patellar instability and result in recurrent patellofemoral dislocations. One of the possible symptoms caused by patella alta can be patellofemoral pain with or without patellar instability. In addition, patella alta is a significant risk-factor for patellofemoral dislocations and anterior knee pain.

Several methods have been described to measure patellar height in the scientific literature [1]: the most commonly used methods as the Insall-Salvati index [2], the Blackburne-Peel index and the Caton-Deschamps index [3, 4]. The patellotrochlear index (PTI) is a novel measure to concretise the contact area between the patellar and trochlear joint surfaces [1].

Distalising tibial tubercle osteotomy (DTTO) is a suitable surgical procedure to treat patella alta. [5, 6]. During the early rehabilitation phase after DTTO, it is common to limit weightbearing and knee flexion with orthosis. In general, the orthosis is used for between 4 and 8 weeks and limited weightbearing is maintained for 4 to 6 weeks to avoid potential implant failure leading to displacement of the osteotomy or non-union. The potential risks of this rehabilitation protocol are restricted knee range of motion (ROM) and muscle weakness, leading to delayed recovery and the possible need for additional procedures.

In our previous, as yet unpublished, retrospective study, we have shown that accelerated rehabilitation is a feasible treatment method after DTTO, and we believe that patient aftercare can be more aggressive than at present. However, to the best of our knowledge, no high-quality randomised controlled trials have been conducted to date on postoperative rehabilitation protocols after DTTO.

Thus, the aim of this randomised controlled trial is to identify the differences between the results of two postoperative rehabilitation protocols. One of the protocols is a typical conservative rehabilitation protocol and other is a novel accelerated rehabilitation protocol.

## Materials and methods

In this is prospective, randomised, controlled, single-blinded, single centre trial, we compare an accelerated rehabilitation protocol with a typical conservative rehabilitation protocol after DTTO (Fig 1 and Table 1). The trial will be reported in accordance with the Consolidated Standards of Reporting Trials (CONSORT) guidelines.

**Fig 1 pone.0304075.g001:**
[figure not shown]
Study flow chart.

**Table 1 pone.0304075.t001:** Study design and assessments.

	Study period					
	Enrolment	Allocation	Post allocation			
Study visit	1	2	3	4	5	6
Timepoint	Preoperative	Surgery day (0)	6 weeks	12 weeks	24 weeks	52 weeks
** Enrolment **						
Eligibility screening	x					
Informed consent	x					
Demographics and medical data	x					
Allocation		x				
** Intervention **						
TT-distalisation		x				
** Assessments **						
BPII score	x		x	x	x	x
KOOS	x		x	x	x	x
Adverse events		x	x	x	x	x

TT-distalisation–distalisation of tibial tubercle; BPII–Banff Patella Instability Instrument; KOOS–Knee Injury and Osteoarthritis Outcome Score.

The hypothesis of the trial is that the novel accelerated rehabilitation protocol will lead to faster recovery and improved functional outcome at 6, 12 and 24 weeks compared with the conservative rehabilitation protocol. The secondary hypothesis is that the complication rate will be similar for both protocols.

The primary outcome in this study will be knee ROM measured at 12 weeks postoperatively. A total difference regardless of the direction of the movement of 10° in full range of movement will be considered significant. The results will be measured with a long goniometer in a standardised manner. Secondary outcomes will be knee ROM measured at baseline, 6, 24 and 52 weeks postoperatively, the Knee Injury and Osteoarthritis Outcome Score (KOOS) and the Banff Patella Instability Instrument (BPII) score measured at baseline, 6, 12, 24 and 52 weeks, and isometric muscle strength measured at baseline, 12, 24 and 52 weeks postoperatively. Regained isometric muscle strength will be measured during follow-up visits and calculated to a ratio compared with a preoperative value. The number of reoperations and complications (failure of fixation and stress-fractures) will be also reported as secondary outcomes. The KOOS questionnaire is an instrument to assess patients’ opinions about their knees and any associated problems. KOOS consists of 5 subscales: Pain, other Symptoms, Function in daily living, Function in sport and recreation and knee related Quality of life. BPII is also a patient-reported outcome measurement instrument. BPII is, however, more specific for patellofemoral problems.

After enrolment, all the patients visit the study physiotherapist. The baseline scores from ROM, isometric muscle strength, KOOS and BPII are recorded during the visit. Randomisation to the allocation groups will be done after surgery.

The ROM measurements are taken with a goniometer, with the patient in supine position. The active ROM is measured as the patient moves the knee in a full range of active flexion and extension. ROM is then measured. Passive ROM is measured in the same supine position. The examiner first moves the knee in a full range of flexion and then in a full range of extension. ROM is then measured. Full ROM is 5º-0º-140º. A ROM of 0º-130º is considered adequate.

The knee extension isometric power measurement is performed with the participant in the sitting position. The isometric power is measured with belts-stabilized dynamometer placed in the support pilar of the treatment table and connected to participants ankle with anchor belt placed 5 cm above the ankle.

The measurement is taken with a dynamometer at three different knee angles 5°, 30° and 90°.

KOOS and BPI are taken before the muscle strength and ROM measurements.

Ethical approval has been obtained from the local health authority. Patients recruited and those patients who declined to take part in the trial but joined the follow-up cohort will provide written informed consent. All data will be deidentified and the results will be published at the group level only. Individual patients will not be identifiable.

The trial is registered in Tampere University Hospital medical research ethics committee ([contact]) on 15.11.2022 with registration number R22072.The trial is registered in ClinicalTrials.gov, Identifier: NCT05854056

### Patient selection

The eligible study population will comprise all consecutive patients aged 15 to 35 years with closed growth plate (physis) who have been referred for DTTO surgery at Pihlajalinna Koskisairaala Hospital, Tampere, Finland. The upper age limit was chosen to minimize the effect of patellofemoral osteoarthritis. As the DTTO procedure can only be planned for skeletally mature patients, the closure of the physis will be evaluated with magnetic resonance imaging (MRI) and plain radiographs. The Greulich and Pyle method will be used to define skeletal age if needed [7].

Only those patients with isolated DTTO or DTTO combined with medial patellofemoral ligament reconstruction will be included in the study. At the initial out-patient ward the treating physician will give the information about the study and ask for written informed consent.

The following criteria will be used for patient selection throughout the study.

❖ Inclusion criteriaSymptomatic patella alta with recurrent dislocation or subluxation. Long-lasting anterior knee pain not responding to rehabilitation.❖ Exclusion criteria➢ Radiographic:Open growth platesIwano [8] grade III and IV changes in patellofemoral jointCaton-Deschamps <1.2 in MRIPTI >30% in MRIHigh grade trochlear dysplasia➢ General:Refuses to participate in the studyAged less than 15 or more than 35 yearsSevere neurological, pulmonal or cardiovascular comorbidities that are contraindications for surgeryLack of adequate co-operationDoes not adequately understand written and spoken instructions in the local language

Those patients who decline to take part in the trial will be asked to join a follow-up cohort as a background population. The patients in this follow-up cohort will be treated “as normal” without allocation, but the follow-up questionnaires will be the same as those given to the randomly assigned population. The patients in the follow-up cohort will also be asked to provide informed written consent.

### Randomisation

Patients will be randomised using a pre-trial random number matrix in block allocation fashion in varying block. We have two stratification factors. First is age (under 20 and 20–35 years) since age has been shown to associate with the main outcome measure. Another stratification factor will be history of the patellar dislocation i.e. group 1- history with at least 1 documented patellar dislocation and group 2-history with no documented patellar dislocation.

Randomisation will be performed using an online randomisation platform (Redcap). After informed written consent has been received and the intervention in the OR performed, the patients will be randomly allocated for rehabilitation. The physician responsible for the intervention or treatment will not participate in the collection of patient outcomes during the follow-up. Patients are encouraged not to reveal the group to the assessor, so assessor will be blinded. The Patients research data will be concealed to Redcap program until the blinded analysis and two versions of discussions has been agreed. After which the group will be revealed. The research coordinator will monitor the study flow. An independent monitoring committee, which was established during our previous randomised controlled trial, will monitor the study.

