### Power analysis

We defined 10 degrees [10] in knee ROM in the primary end-point as a clinically relevant difference we would not like miss. We estimated a common standard population deviation of 20 degrees for knee ROM in both groups. Based on unadjusted t-test (TrialSize package in R), we need 63 patients per group to have a power of 80% with 5% type I error level. With this age group, the estimate of loss to follow-up rate will be set to 5% and will result in a total of 132 patients participating in the trial.

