### Statistical analysis

Study analysis will be done using mixed linear model allowing for repeated measures in longitudinal setting. All continuous variables will be analyses in this fashion. Each outcome variable will be the dependent variable and patient the random factor. Study group and time point will be included as fixed factor. Stratification variables are included as covariates in the analysis. If baseline value for the dependent variable (i.e. ROM) is available, it will be included also as a covariate. Treatment effects at each time point are the estimated marginal means for time point and study group interaction term. Satterthwaite method is used to estimate degrees in freedom in these analyses. No imputation is needed as liner mixed model is used and a full data set will be used in the analyses. Logistic regression is used to analyse binary outcome. Adjusted risk difference at each time point will be reported for complications and reoperations. All analyses will done with RStudio with suitable packages (i.e. *lmer* and *emmean*).

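### The primary model uses age only as two bands, although the protocol calls age prognostic; adding age in years could recover a little precision

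*Protocol article*

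**What the plan says.** **Age as a factor.** The Randomisation section names two stratification factors: age in two bands (under 20, and 20 to 35) and documented patellar dislocation (yes or no). Age was chosen "since age has been shown to associate with the main outcome measure". Patient selection sets the eligible range at 15 to 35 years.

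**The model.** The Statistical analysis section specifies a linear mixed model with study group and time point as fixed factors and patient as random factor. On covariates it says "Stratification variables are included as covariates in the analysis", and it adds the baseline value of the outcome where available, naming ROM as the example. Age in years is not mentioned.

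**Timing.** Demographic data are collected at enrolment (Table 1). Allocation comes after the operation: "After informed written consent has been received and the intervention in the OR performed, the patients will be randomly allocated for rehabilitation". Age and the procedure performed are therefore both fixed before randomisation.

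**Surgery.** "Only those patients with isolated DTTO or DTTO combined with medial patellofemoral ligament reconstruction will be included in the study" The model has no term for reconstruction.

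**The concern.** A protocol that gives prognostic value as its reason for stratifying on age, and then analyses age only as a two-level factor, may discard part of that value. All patients from 20 to 35 share one age term, although that band covers 15 of the 20 eligible years. If ROM at 12 weeks changes with age inside the band, the variation goes into the residual, widens the confidence interval for the treatment difference and lowers power. Randomisation keeps the comparison fair either way, so only efficiency is at stake.

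**Working it through.** **1. The plan's own figure.** The Power analysis gives the inputs: "We defined 10 degrees [10] in knee ROM in the primary end-point as a clinically relevant difference" and "We estimated a common standard population deviation of 20 degrees for knee ROM in both groups". With two-sided alpha of 5% and 80% power, n per group = 2 × (1.960 + 0.842)² × (20/10)² = 62.8, so 63. This agrees with "we need 63 patients per group to have a power of 80% with 5% type I error level". Allowing for dropout, 126/0.95 = 132.6, against the 132 stated, which is close enough. The calculation is an unadjusted t-test and does not rely on any covariate.

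**2. What the two bands keep.** Assume a linear age effect and age uniform on 15 to 35.
- Total variance of age: 20²/12 = 33.3.
- A quarter of patients are under 20 (mean 17.5) and three quarters are 20 or over (mean 27.5). Between-band variance: 0.25 × 0.75 × 10² = 18.75.
- Share kept: 18.75/33.3 = 56%.

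In simulations with ages skewed towards the young end (36% to 40% under 20), the share is 60% to 61%.

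**3. Effect on power.** Let r be the correlation of age with 12-week ROM. The protocol gives no value, so 0.2, 0.3 and 0.4 are assumptions. Baseline ROM and dislocation history are already in the model, so r is read as conditional on them, and the SD of 20° as the SD left after them. The bands explain 0.5625 × r² of the variance and age in years explains r². The standardised effect is 0.5/√(1 − R²). With 132 × 0.95 = 125.4 patients, or 62.7 per arm, the noncentral t gives:

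| Assumed r | R², bands | R², years | Power, bands | Power, years | Gain (points) | Worth, of 126 patients |
|---|---|---|---|---|---|---|
| 0.2 | 0.0225 | 0.04 | 80.2% | 80.9% | 0.7 | 2.3 |
| 0.3 | 0.0506 | 0.09 | 81.3% | 82.9% | 1.6 | 5.2 |
| 0.4 | 0.0900 | 0.16 | 82.9% | 85.8% | 2.8* | 9.7 |

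*From unrounded values, 82.94% and 85.79%.

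The last column is 126 × [1 − (1 − R² years)/(1 − R² bands)]. For r = 0.3 this is 126 × (1 − 0.91/0.9494) = 5.2.

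**4. Precision.** The half-width of the 95% confidence interval is about 1.96 × 20 × √(1 − R²) × √(2/62.7). For r = 0.2, 0.3 and 0.4 it falls from 6.92° to 6.86°, from 6.82° to 6.68°, and from 6.68° to 6.42°.

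**5. If the effect is not linear.** If the association is a step at 20, the band already carries all of it and age in years adds nothing.

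**The case against.** The strongest case against is that nothing here is an error. Adjusting for both stratification factors and the baseline value is a conventional, valid set that matches the randomisation. The trial is sized on an unadjusted test, so any gain from covariates is surplus. The protocol gives neither the strength nor the shape of the age association, and the 56% depends on linearity and an even age spread. Baseline ROM may already absorb part of any age effect. All of this stands. It is why the loss can only be called possible, and why the correlation has to be read as conditional on what the model already holds. It does not remove the point: the protocol itself calls age prognostic and lists the form in which age enters.

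A reader might also infer that omitting ligament reconstruction costs precision. It precedes allocation, so it would be a valid covariate. Dislocation history is an incomplete stand-in, since patients with subluxation but no documented dislocation are eligible. The documents do not support more than that. No section links reconstruction to 12-week ROM, nor says what share of patients receive it. Dislocation history, already in the model, covers part of it. A sizeable gain appears only if reconstruction is assumed to shift ROM by 10°, which equals the trial's whole target difference. With an assumed 5° effect in half the patients and a correlation of 0.7 with dislocation history, power at 63 per arm moves only from 80.1% to 80.4% (normal approximation). Table 1 does not list reconstruction as a recorded item, so it cannot be assumed to be in the trial data.

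**Conclusion.** The point holds as an optional, low-cost improvement. The model as written uses age only in two bands although the protocol calls it prognostic, so some precision may be lost. Under a linear effect, uniform age and a conditional correlation of 0.2 to 0.4, age in years is worth about 0.7 to 3 points of power, or about 2 to 10 patients of 126. The gain shrinks towards zero if the effect is weaker or is mainly a step near 20. These correlations are assumptions and do not come from the protocol.

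It would be wrong to infer that the planned analysis is biased or invalid, that the stated power depends on this change, or that a loss of a given size has been shown.

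**What to change.** In the Statistical analysis section, keep the two stratification factors and the baseline value, and add age in years as a continuous fixed covariate in the mixed model for ROM and the other continuous outcomes. Specify it before unblinding so that it cannot look data-driven. The cost is one sentence and about one degree of freedom. Age follows from information already needed for eligibility and stratification, and the sample size need not change. If a separate statistical analysis plan already does this, no action is needed.

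Reconstruction (yes or no) may be added as an optional covariate if the investigators have grounds to expect that it predicts ROM. It should then be listed among the recorded data items.

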### Surgical treatment

Operative treatment will be performed by trained and experienced knee surgeons. The surgeons’ skills and number of procedures will be reported according to the criteria given by the Consort Group [9].

The aim of the surgical treatment is to normalise the biomechanics of the patellofemoral joint. The operation will start with an arthroscopic examination to verify patella alta position. The high-positioned patella in relation to the trochlea will be documented and an approximation made of the required distalisation for adequate cartilage contact between the patella and the trochlea. Thereafter, a 5–7 cm mid-line incision will be made at the tibial tubercle. The gracilis graft will be harvested from the same incision if needed for medial patellofemoral ligament reconstruction. The lateral aspect of the tibial tubercle will be exposed. The proximal distalisation cut will be made in AP direction at 70º angle at a minimum of 6–7 cm distally from the tibial tubercle. The distal AP cut will be done according to preoperative measurements taken from imagining data and the arthroscopic findings of the patient. The bone block will be removed to allow distalisation of the tubercle. Furthermore, the tubercle will be mobilised with chisels to allow the distalisation of the tubercle. The distalisation is at least 5 mm, usually even more. The osteotomy will be fixed with two 4.5 mm AO screws. The appropriate localisation of the fixation and patella will be confirmed with fluoroscopy.

### Rehabilitation

Patients will be randomised in two rehabilitation groups. Patients in both groups will be guided by in-ward physiotherapists and will be given written physiotherapy guidelines for both instructed physiotherapy and self-guided exercises. After discharge from the hospital, patients will be referred to physiotherapy for further guidance. Both groups will start preliminary exercises from the first postoperative day to reduce oedema in the operated lower limb. For the detailed rehabilitation guidelines, please see Table 2.

**Table 2 pone.0304075.t002:** The rehabilitation guidelines.

Elements of physical therapy	Group 1 Accelerated rehabilitation	Group 2 Conservative rehabilitation
Antioedema knee, calf, leg	Day 1	Day 1
Knee brace, ROM limitations	No	6 weeks
Weight-bearing limitations	No, crutches are recommended for 4 weeks.	4 weeks limb weight, followed by half body weight till week 6
Active exercises. Functional exercises.	1 week	8 weeks
Active dynamic strengthening exercises.	5 weeks	8 weeks
Closed chain exercises for muscle strengthening.	8 weeks	8 weeks
Muscle endurance and neuromuscular control, progress strengthening exercises, jogging	12 weeks	12 weeks

